### Expected duration of trial: end of study definition

Patient recruitment is expected to take approximately 24 months (including interim reviews), and follow-up will continue until the last recruited patient completes their 12 months follow-up unless the trial is terminated earlier for futility. The trial will be closed when all participants have made their final follow-up visit, the data are entered into the database and all queries resolved and the database locked. All serious adverse events (SAEs) will be followed up for a further 30 days after the stopping of the trial (last patient’s final 1 year follow-up visit date) or until resolution.

### Safety evaluation and reporting of adverse events

The Investigator or clinician with delegated authority will review all clinical laboratory reports and will sign and date them on the day of review. If there are any findings outside the normal range, the investigator will confirm whether the result is clinically significant or not. Any laboratory report indicated as being clinically significant will be recorded on the Adverse Event section of the CRF.

All adverse events will be recorded from time of consent. However, as Mirococept is administered to the kidney ex vivo and is cytotopic, i.e. cell membrane associated, very little is expected to enter the systemic circulation. The safety of Mirococept has been demonstrated in preclinical studies as well as in phase I and II clinical trials. In the phase I randomised, double-blind, placebo-controlled, dose escalation study, doses of up to 100 mg given to healthy men as a single intravenous (IV) infusion were tolerated well. There were seven dose levels, 2, 5, 10, 20, 40, 70 and 100 mg, and six subjects participated in each dose level, four subjects receiving active drug and 2 receiving Pbo. There were no deaths or SAEs and the number of treatment-related AEs was low up until the 100 mg Mirococept dose. With 100 mg IV infusion there were increased events in three out of four subjects receiving the active medication. For this dose level, the most common complaints were general disorders (fatigue, headache) and nausea with one occurrence of pyrexia. The lack of any consistent pattern in the AEs for doses lower than 100 mg Mirococept indicated good tolerability. There were no treatment-related changes in vital signs or clinical laboratory parameters. The plasma elimination half-life in healthy subjects was approximately 3 h, and for doses below 10 mg there was no apparent inhibition of systemic complement activation. A pilot phase II study conducted in 12 patients using a dose of 10 mg of Mirococept perfused into donor human kidneys which were then transplanted also showed that this agent and mode of administration was well tolerated. More than 80% of the drug was retained in the graft and no inhibition of circulatory complement was detected. The starting dose level of 10 mg was based on animal data [6, 20] and was found to be safe in phase I and pilot phase IIa studies [21].

In the present protocol, we do not expect more than approximately 20% of the maximum dose administered to the graft to reach the systemic circulation. At the doses proposed (5–25 mg), this exposure lies in the range of 1–5 mg of drug. Therefore, we do not consider drug-related AEs to be likely.

### Statistical analysis

#### Basic power calculation

We will consider the use of Mirococept superior to standard cold perfusion if the upper boundary of the 95% confidence interval for the absolute DGF risk difference includes the minimum considered clinically significant (10%). All calculations have been made presuming an absolute risk of DGF of 35% [2] and thus expecting it to drop to at least 25% in the treatment group.

Using an asymmetric two-sided group sequential design, with 80% power and 5% type I error [24], the maximum sample size is 283 transplant pairs, a total of 566 patients. Based on this sample size calculation, we used a total sample size of 560 to perform a simulation study under different scenarios of dose response to optimise the performance of the adaptive design and determine the dose allocation rules (results given in Additional file 5). The power to detect differences in the response between the accumulated Pbo patients and the dose to which the largest number of patients were allocated was above 0.80 for three out of the four scenarios of dose response, where the fourth scenario was one where there was no effect. Under the absence of an effect, only 5% of the simulated trials found a significant effect, which is consistent with a 5% type I error.

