### Recruitment in cohorts

Patients will be enrolled in cohorts of *N* = 80 with a maximum number of 7 cohorts (maximum number of transplants = 560). Each cohort will be randomised to one of two groups, Pbo or one dose of Mirococept. As originally planned, the first cohort will be randomised to Pbo or 10 mg of Mirococept. After the completion of each cohort, an interim analysis will be carried out in order to evaluate the dose allocation for the next cohort (Fig. 2: recruitment cohorts). Based on the data from previous studies, we will work with five possible doses: 5 mg, 10 mg, 15 mg, 20 mg and 25 mg.

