### Randomisation

Recruiting site personnel will be responsible for randomisation of individual patients through the described process. Patients will be randomised to treatment or Pbo with an allocation ratio of (Pbo:drug) 1:2 (i.e. 27 Pbo/53 drug per cohort). Randomisation uses minimisation for the following factors:□ Centre□ Donation after Circulatory Death (DCD) or Donation after Brain Death (DBD)□ Machine pump use

Once ensuring all inclusion and none of the exclusion criteria are met and written informed consent is obtained, the patient must be registered on the MACRO trial database and is assigned a unique patient identifier. The patient can then be randomised, with this patient ID, via SealedEnvelope, an independent web-based company that will be accessible to all the centres via the Internet (https://www.sealedenvelope.com/empirikal/). In the event that a pack number is assigned, but the transplant does not go ahead, the pack is quarantined, in the area predesignated for quarantined kits, until it can be reassigned for use.

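### The superiority sentence gives no direction and never requires the interval to exclude zero, so it contradicts the 5% type I error and 80% power stated beside it

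*Protocol article*

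**What the plan says.** In the Protocol article, section Basic power calculation, Mirococept is to be considered superior "if the upper boundary of the 95% confidence interval for the absolute DGF risk difference includes the minimum considered clinically significant (10"%). This is the article's only definition of superiority. It attaches no sign to the risk difference and sets no condition on the lower limit or on zero.

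The same section presumes a 35% DGF risk on placebo, "thus expecting it to drop to at least 25% in the treatment group". It claims 80% power and 5% type I error for an asymmetric two-sided group sequential design, from which "the maximum sample size is 283 transplant pairs, a total of 566 patients". It then reports a simulation in which "Under the absence of an effect, only 5% of the simulated trials found a significant effect". The simulated power compares all placebo patients with the most-allocated dose.

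Two other sections bear on the point. Interim analysis and dose allocation treats a larger placebo-minus-drug difference as benefit. Final data analysis makes a logistic regression the main analysis of DGF and does not mention the interval rule.

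**The concern.** A superiority criterion has to rule out no effect. Take the difference as placebo minus drug, so that positive values favour Mirococept. The rule then asks only that the most optimistic end of the interval reach 10 points. An interval from −8 to +12 points would pass, and less precise data pass more easily. Take the difference the other way, and the natural reading is that the upper limit must be at or below −10 points. The whole interval must then show at least the benefit the trial was planned to detect, which almost never happens when that benefit is the true effect.

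At stake is the trial's primary conclusion. Someone applying the sentence literally could call a null result a success or an effective drug a failure, depending on a sign that the sentence does not give.

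**Working it through.** **Inputs.** DGF risk 35% on placebo and 25% on drug under the alternative (Basic power calculation). Seven cohorts of 80 (Recruitment in cohorts), each with 27 placebo and 53 drug (Randomisation). This gives 7 × 27 = 189 placebo and 7 × 53 = 371 drug patients. A single dose used in three or four cohorts has 159 or 212. The 1:1 sizing is 283:283. The Wald interval and the absence of futility stopping are assumptions of this check.

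**The plan's own sample size.** Per-arm n = [z_α √(2 × 0.30 × 0.70) + 0.842 √(0.35 × 0.65 + 0.25 × 0.75)]² / 0.10².

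- 5% in one direction (z = 1.645): (1.066 + 0.542)² / 0.01 ≈ 259, or 279 with continuity correction. The stated 283 is 259 × 1.09, a plausible group sequential inflation.
- Two-sided 5% (z = 1.96): (1.270 + 0.542)² / 0.01 ≈ 329, already above 283 before any inflation.

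So 283 is approached only with the 5% spent in one direction. The boundaries are not shown, so this cannot be confirmed exactly.

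**Reading 1: placebo minus drug, upper limit at least 10 points.** With no effect, SE = √[0.35 × 0.65 × (1/n₀ + 1/n₁)]. The rule is met when the observed difference is at least 0.10 − 1.96 SE, which has probability 1 − Φ[(0.10 − 1.96 SE)/SE].

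| Placebo : drug | SE | Observed benefit needed | Inert drug passes |
|---|---|---|---|
| 283 : 283 | 0.0401 | 2.1 points | 29.7% |
| 189 : 371 (doses pooled) | 0.0426 | 1.6 points | 35.0% |
| 189 : 212 (one dose) | 0.0477 | 0.6 points | 44.6% |
| 189 : 159 (one dose) | 0.0513 | −0.1 points | 50.5% |

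Example at 189:371: 0.2275 × (1/189 + 1/371) = 0.001817, so SE = 0.0426. The threshold is 0.10 − 0.0835 = 0.0165, and 0.0165/0.0426 = 0.386, giving 35.0%.

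At a true 10-point benefit this reading passes 97.5% of the time at any sample size, because the threshold always lies 1.96 SE below the true value. It therefore cannot be what the 80% power calculation rests on.

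**Reading 2: drug minus placebo, upper limit at or below −10 points.** At a true 10-point benefit the estimate must exceed the true value by 1.96 SE, which has probability 2.5% at any sample size.

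**Reading 3: the interval contains 10 points.** The null pass rates are the same to three decimals at the sizes above. A result whose interval lay wholly beyond 10 points would fail.

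**Rule that excludes zero.** If the lower limit of placebo minus drug must exceed 0, an inert drug passes 2.5% of the time in a fixed comparison. A 40,000-run reconstruction of the cohort design without futility stopping gave 3.6% for the most-allocated dose. Power is Φ(0.10/SE − 1.96), with SE = √(0.2275/n₀ + 0.1875/n₁):

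- 283:283: SE = 0.0383, Φ(0.65) ≈ 74%.
- 189:371 pooled: SE = 0.0413, Φ(0.46) ≈ 68%.

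**The case against.** The strongest reply is that this sentence is not the test that was simulated or will be run. It sits under the power calculation, not under Final data analysis. The 5% null result and the power to detect differences both describe an ordinary significance test, and the main analysis is a logistic regression. This stands. A reader might infer that the trial would declare an inert drug superior in 35–50% of cases, or about half the time. The documents do not support that, for three reasons:

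- The sentence gives no direction. The placebo-minus-drug sign has to be borrowed from the dose-allocation text, and the opposite sign leads to almost no trial passing.
- One half is the top of the range and applies to a single dose with about 159 patients. Pooling all doses gives 35%, and the 1:1 sizing gives 30%.
- The reconstruction of the cohort design gives 49% for the most-allocated dose, but without a futility stop. The article allows one after two consecutive cohorts at 25 mg (under Handling of missing data in secondary outcomes) and gives no cut-off. Depending on the cut-off, and on whether stopped trials can still be declared superior, the rate could be lower or higher.

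The reply does not remove the defect. The sentence states in so many words when the drug will be considered superior, and the regression paragraph neither repeats nor corrects it.

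**Conclusion.** The superiority sentence is mis-specified and contradicts the operating characteristics stated in its own section. On the placebo-minus-drug reading, the null pass rate is about 30% to 50%, against a stated 5%. On the opposite reading, power at the planned effect is 2.5%, against a stated 80%. These figures rest on 35% DGF in both arms under the null, Wald intervals, fixed sample sizes and no futility stopping. They describe the rule as worded. They do not show that the final analysis would err at those rates, because an ordinary significance test was probably intended. The correction is still needed, since the sentence governs the primary conclusion.

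**What to change.** Replace the sentence with: *Mirococept is superior if the two-sided 95% CI for the absolute DGF risk difference (Pbo minus drug), for the same comparison as the primary analysis, lies wholly above 0; the estimate and CI are then compared with 10 percentage points to describe clinical relevance.*

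The edit is one sentence and needs no new data. Any analysis plan, which is not shown here, should be checked for the same wording. There is a small downside to state openly: a two-sided 95% interval above zero spends 2.5% in the favourable direction, whereas the 283 figure appears to spend 5%. With power at about 74% (283 per arm) or 68% (189:371 pooled), the article should either restate the 80% or make its one-directional alpha explicit.

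### The 283 pairs give 80% power only if essentially the whole 5% is spent on the efficacy side at 1:1; for 35% v 25% the 1:2 trial has at most about 69% power two-sided (79% one-sided)

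*Protocol article*

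**What the plan says.** All references are to the Protocol article.

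- *Basic power calculation* takes a 35% placebo risk, "thus expecting it to drop to at least 25% in the treatment group". The design is described as group sequential, two-sided and asymmetric. Its size is given in these words: "with 80% power and 5% type I error [24], the maximum sample size is 283 transplant pairs, a total of 566 patients".
- The same section judges superiority on "the upper boundary of the 95% confidence interval for the absolute DGF risk difference".
- It then continues: "we used a total sample size of 560 to perform a simulation study under different scenarios of dose response". The simulated comparison is all placebo patients against the dose that received most patients. Its power "was above 0.80 for three out of the four scenarios of dose response", the fourth scenario being no effect. Details are in Additional file 5, which is not shown.
- *Randomisation* fixes the ratio: "Patients will be randomised to treatment or Pbo with an allocation ratio of (Pbo:drug) 1:2 (i.e. 27 Pbo/53 drug per cohort".
- *Recruitment in cohorts* and *Interim analysis and dose allocation* give at most seven cohorts of 80, one active dose per cohort, and five doses among which the allocation moves.

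**The concern.** The maximum sample size of a group sequential design cannot be smaller than the fixed sample for the same error rates, yet 283 is below the fixed two-sided 5% figure. The word pairs also implies equal arms, while the trial randomises 1:2 and spreads its active patients over doses.

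The 10-point difference matters because the article treats it as the smallest clinically important one. If power at that difference is well under 80%, a real benefit of that size is missed more than one time in five. A null result could then be misread as good evidence of no benefit.

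**Working it through.** **Inputs.** p1 = 0.35, p2 = 0.25, 80% power, 5% type I error, 283 per group, 560 simulated (all *Basic power calculation*). 27 placebo and 53 active per cohort (*Randomisation*). Seven cohorts (*Recruitment in cohorts*), so 7 × 27 = 189 placebo and 7 × 53 = 371 active.

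**1. Fixed 1:1 sample per arm.** n = [z_a√(2p̄q̄) + z_b√(p1q1 + p2q2)]² / (p1 − p2)², with p̄ = 0.30, so the two roots are 0.6481 and 0.6442, and z_b = 0.8416.
- Two-sided 5%: (1.960 × 0.6481 + 0.8416 × 0.6442)² / 0.01 = 328.5. The unpooled form, (1.960 + 0.8416)² × 0.415 / 0.01, gives 325.7.
- One-sided 5%: (1.645 × 0.6481 + 0.8416 × 0.6442)² / 0.01 = 258.6. Unpooled: 256.6.

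**2. Reproducing 283.** 283/328.5 = 0.86, so two-sided 5% is excluded. 283/258.6 = 1.094 and 283/256.6 = 1.103, a plausible sequential inflation of about 10%. Numerical integration was used with 5% on the efficacy side, a binding futility bound spending 20%, and O'Brien-Fleming-type spending. It gives 277, 284 and 289 per arm for three, five and seven looks. With 2.5% on the efficacy side, the same design needs about 350 to 362. Boundary type and number of looks are assumptions.

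Solving the pooled formula in step 1 for n = 283 gives z_a = (0.1√283 − 0.5422)/0.6481 = 1.759, or 3.9% on one side. So the efficacy side must carry at least about 3.9% of the 5% with no sequential inflation at all, and essentially the whole 5% once inflation of about 10% is allowed.

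**3. Power at 35% v 25%.** Power = Φ{(0.10 − z_a s0)/s1}, with s0 = √[p̄q̄(1/n1 + 1/n2)], p̄ the size-weighted mean, and s1 = √(p1q1/n1 + p2q2/n2).
- 283 v 283: s0 = 0.03852, s1 = 0.03829. Two-sided, (0.10 − 0.0755)/0.03829 = 0.640, so 74%. One-sided 5%, 83% as a fixed test.
- 189 v 371: p̄ = 0.2838, s0 = 0.04029, s1 = 0.04134. Two-sided, (0.10 − 0.0790)/0.04134 = 0.509, so 69%. One-sided 5%, (0.10 − 0.0663)/0.04134 = 0.816, so 79%.
- 280 v 280 gives 73% two-sided, so the 1:2 ratio costs about 4 points.

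**4. One dose against 189 placebo, same formula.**

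| Cohorts on the dose | Active n | Two-sided 5% | One-sided 5% |
|---|---|---|---|
| 7 | 371 | 69% | 79% |
| 5 | 265 | 64% | 75% |
| 4 | 212 | 59% | 71% |
| 3 | 159 | 52% | 65% |

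**5. Reconstruction of the adaptive rules.** Start at 10 mg, cut-offs −0.01 and 1.5, seven cohorts of 27/53, no early stop. The final z test compares all placebo with the most-used dose, with ties going to the higher dose (20,000 runs). Effective doses are set at exactly 25% and the others at 35%.

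| Effective doses | Two-sided 5% | One-sided 5% |
|---|---|---|
| All | 65% | 76% |
| From 10 mg | 64% | 75% |
| From 15 mg | 58% | 69% |
| From 20 mg | 54% | 66% |

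With every dose at 20% (a 15-point effect), two-sided power is 94%.

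**6. Effect detectable with 80% power, two-sided.** 11.3 points with 371 on the dose, 13.6 points with 159.

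**The case against.** Three stronger readings are tempting, and the document does not support them.

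- *That 283 is an arithmetic slip.* It is recovered closely by an asymmetric design with 5% on the efficacy side and futility stopping. On that basis, 80% at 1:1 is right and the fixed counterpart is 259, not 329. The undeclared alpha split is the fault.
- *That the plan ignores the split over doses.* Only the 566 calculation does. The same section goes on to simulate all placebo against the most-used dose.
- *That the simulated power above 0.80 is false.* Its dose-response scenarios are not shown. The article allows a fall to 25% or lower, and at 20% the reconstruction passes 0.80 easily. One can say only that 0.80 seems to need more than a 10-point effect.

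Two further objections have weight. *Final data analysis* describes a logistic regression of Mirococept use with covariates and does not restrict it to one dose. It can be read as pooling all 371 active patients, so the single-dose figures may not describe the main analysis. The powers above are also unadjusted. Next, on the one-sided 5% reading the pooled 1:2 design reaches 79%, a negligible shortfall as a fixed test.

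What stands: the one-sided reading is not declared and conflicts with a decision on a 95% interval. On the two-sided reading no grouping reaches 80% at 10 points. A single dose that received at most five of the seven cohorts falls short on either reading.

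**Conclusion.** The point holds. The stated 80% is not a property of the 1:2 design at 35% v 25% when tested two-sided at 5%. Power there is about 69% with all active patients pooled and every dose fully effective, so a true 10-point benefit would be missed about 31% of the time instead of 20%. For the most-used dose, power is about 54% to 65% two-sided, or 66% to 76% one-sided.

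The pooled figures follow from printed inputs and an unadjusted test. The single-dose figures rest also on the assumed dose-response shapes and tie rule. No conclusion is drawn about the sponsor's own simulation beyond the need to see its power at exactly 25%.

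**What to change.** 1. State how the 5% is divided between the efficacy side and the other side, and make it agree with the 95% interval used for the decision.
2. Replace the 283 pairs, or label them as a one-sided 5%, 1:1 figure if that is what they are.
3. Restate power for 1:2 allocation (189 v 371) at 35% v 25%, both with all active patients pooled and for the most-used dose. Take the latter from the sponsor's own simulation, and give the effect sizes behind the scenarios with power above 0.80.
4. Add the effect detectable with 80% power. Two-sided and unadjusted, it is about 11 to 14 points, for 371 down to 159 patients on the dose.

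The cost is a less favourable power statement. No extra patients are needed, and allocation and dose rules stay as they are.

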#### Interim analysis and dose allocation

As discussed earlier, patients will be recruited in cohorts of *N* = 80 with a maximum number of 7 cohorts. Five possible doses will be assessed: 5 mg, 10 mg, 15 mg, 20 mg and 25 mg. The adaptive allocation will be based on a *t* test-like statistic that compares the difference between response (accumulated) at the current dose with the mean response at Pbo plus our target difference 0.10 [23]. In brief, the current dose is repeated if the current estimated difference in responses between dose and Pbo (scaled by the variance) is close to the target 0.10, and changed if otherwise (Fig. 2: recruitment cohorts). Simulation studies (Additional file 5) showed that the following allocation rules provided optimal performance:
*If t statistic < –0.01*: *Increase by one dose (e.g. from 10 mg to 15 mg)*

*If –0.01 < t statistic < 1.5*: *Repeat the current dose (e.g. keep 10 mg)*

*If t statistic > 1.5*: *Decrease by one dose (e.g. from 10 mg to 5 mg)*

Note that a *t* statistic = 0 implies a difference in the rate of DGF between the drug and Pbo groups of 0.10, the minimum clinically significant; a positive *t* statistic implies that the difference in DGF rate between Pbo and the drug is larger than 0.10, and a negative *t* statistic implies that the difference is lower than 0.10.

### Final data analysis

The main analysis of the primary endpoint will consist of a logistic (binary) regression to examine whether the use of Mirococept as compared to standard cold storage, in the context of other relevant covariates, influences the risk of DGF. The same procedure will be applied to binary secondary endpoints. A linear regression will be used for secondary endpoints measured on a continuous scale (e.g. GFR), using a log transformation when the distribution deviates from normality or for time measures (e.g. duration of DGF). For the analysis of graft survival, the comparison between the two groups will be carried out using hazard ratios calculated from a Cox proportional-hazards model, adjusted by the relevant covariates.

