### Outcome measurements

#### Primary outcome

The primary outcome is DGF, defined as the requirement for dialysis during the first week after transplantation.

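### Log-linear regression is a poor choice for duration of DGF: at the planning rates 65-75% of patients have no DGF, so the comparison either conditions on the primary outcome or rests on an arbitrary offset

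*Protocol article*

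**What the plan says.** Duration of DGF is one of the secondary outcomes (Secondary outcomes). It is listed without a definition, an analysis population or a value for patients who never have DGF.

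The method is in Final data analysis, which assigns continuous secondary endpoints to linear regression and gives this rule for transforming them: "using a log transformation when the distribution deviates from normality or for time measures (e.g. duration of DGF"). Duration of DGF is thus the article's own example of a time measure to be logged. No offset, two-part model or rank method is mentioned.

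DGF is itself the primary endpoint: "The primary outcome is DGF, defined as the requirement for dialysis during the first week after transplantation". The planning rates are in Basic power calculation: "All calculations have been made presuming an absolute risk of DGF of 35" per cent on placebo, with the rate in the drug arm put at 25%.

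**The concern.** DGF occurs after randomisation, and it is the event the drug is meant to prevent. A patient without DGF has a duration of zero, whose log does not exist, or no duration at all. On either reading, a plain log-scale regression can be fitted only to patients with DGF. Randomisation does not balance the arms within that subset, because treatment affects who enters it.

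If the drug prevents mainly mild cases, the DGF patients left in the active arm are on average the more severe ones. The ratio of durations can then point the wrong way, or shrink towards 1, although no patient's DGF has been lengthened. What is at stake is the interpretation of one secondary endpoint.

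**Working it through.** **Inputs from the protocol article**
- DGF rates of 35% (placebo) and 25% (drug), from Basic power calculation.
- "allocation ratio of (Pbo:drug) 1:2 (i.e. 27 Pbo/53 drug per cohort"), from Randomisation.
- "maximum number of transplants = 560", in 7 cohorts of 80, from Recruitment in cohorts.

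The article gives no figure for the duration analysis, so there is none to reproduce. The sample size for the primary endpoint is neither used nor disputed here.

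**Step 1. Who remains under a plain log.** Full enrolment gives 7 × 27 = 189 placebo and 7 × 53 = 371 active patients, 560 in all.
- With DGF: 189 × 0.35 = 66 placebo and 371 × 0.25 = 93 active, about 159 patients.
- Without DGF: 189 × 0.65 + 371 × 0.75 = 122.9 + 278.3 = about 401 of 560 (72%).

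Applying 25% to every active patient is an assumption. The article plans up to five doses and does not state a rate for each.

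**Step 2. Bias when no remaining duration changes.** Assume log-duration among placebo DGF patients is normal with SD σ. The article gives no σ, so I take 0.5 to 1.0. The drug prevents 10 of every 35 cases.
- *Prevention unrelated to severity.* The remaining distribution is unchanged, so the ratio is 1.00.
- *Only the shortest 10 of 35 prevented (the extreme case).* The 10/35 quantile of the standard normal is z = −0.566. The mean above it is φ(z)/(25/35) = 0.476. The active:placebo geometric-mean ratio is exp(0.476σ): 1.27 at σ = 0.5, 1.46 at 0.8 and 1.61 at 1.0.
- *Size against its standard error in the extreme case.* The truncated variance is 1 + z × 0.476 − 0.476² = 0.504, in units of σ². The standard error is √(1/66 + 0.504/93) = 0.143σ, so the artefact is 0.476/0.143 = 3.3 standard errors for any σ.

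**Step 3. A latent-severity model.** Assume standard normal severity, with DGF above the threshold 0.385 (35%), log-duration rising by 0.6 per unit of severity, and 7 days at the threshold. The mean severity of placebo DGF patients is 1.058. The log SD among them works out at about 0.32, below the range in step 2.
- *Mildest cases prevented, other durations unchanged.* The active threshold becomes 0.674 (25%) and mean severity 1.271. The ratio among DGF patients is exp(0.6 × (1.271 − 1.058)) = 1.14. Mean duration over all patients falls from 3.9 to 3.1 days.
- *Every patient's severity lowered by 0.674 − 0.385 = 0.289.* A patient who has DGF under either treatment has it shortened by the factor exp(−0.6 × 0.289) = 0.84. The ratio among DGF patients is exp(0.6 × (1.271 − 0.289 − 1.058)) = 0.96. A 16% shortening therefore appears as about 4%. Mean duration over all patients falls from 3.9 to 2.6 days, about 32%; most of that fall is lower incidence, since 25/35 = 0.71.

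**Step 4. Using an offset instead.** In the mildest-cases scenario of step 3, log(duration + c) in all patients gives these ratios:

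| c (days) | ratio |
|---|---|
| 0.01 | 0.51 |
| 0.1 | 0.65 |
| 0.5 | 0.76 |
| 1 | 0.81 |

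The data are the same in each row; only the constant differs.

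**The case against.** **The article does not say that patients without DGF are dropped.** This stands. It does not set their duration to zero either. A reader might infer that the analysis must discard them, but that follows only for a plain log. A log with an offset is still a log transformation and keeps everyone. It does not rescue the method, because the result then depends on the constant (step 4) with most values tied at one point.

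**Zero handling, the analysis set and the coding of primary non-function belong in an analysis plan.** Their absence from an article is not the point, and I make no finding on primary non-function. The point is that the article names a method for this endpoint, and that method fits it poorly however the details are filled in.

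**Time-to-event outcomes are to get survival analysis with censoring.** The section on missing data in secondary outcomes says so, but it does not name duration of DGF, which Final data analysis assigns to log-linear regression.

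**Duration among DGF patients is an acceptable severity description, read beside DGF incidence.** True as description. Final data analysis, however, uses the regression as its method for analysing secondary endpoints, not as a descriptive summary.

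**The 27-61% lengthening is a worst case.** This stands. It needs the drug to prevent exactly the shortest cases, and the lognormal shape and SD are assumed. Other assumptions give 1.14, 1.00 or 0.96.

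**Conclusion.** The concern holds as a badly chosen method for one secondary endpoint. At the planning rates, 65% of placebo and 75% of active patients have no DGF. A log-scale regression then either compares about 66 with 93 patients selected by the primary outcome, or needs an offset that drives the estimate.

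The size and direction of the bias are not known in advance. The ratio among DGF patients is 1.00 when prevention is unrelated to severity and reaches 1.27-1.61 in the extreme case (assumed log SD 0.5-1.0). Under the assumed uniform severity shift it is about 0.96, where the shortening in patients who have DGF either way is 16%. The counts assume 25% DGF in all active patients and full enrolment of 560.

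A reader might infer that the trial will show Mirococept prolonging DGF because it works. The documents do not support that: it is one scenario, and nothing in them says which cases would be prevented. Nor does being first in the list give the endpoint priority, since no hierarchy is stated. The primary analysis, sample size and dose-allocation rules are untouched.

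**What to change.** Replace log-linear regression for this endpoint with a comparison in all randomised and transplanted patients. Score days of dialysis dependence, with 0 for no DGF and primary non-function or death on dialysis ranked worst. Compare the arms by a proportional-odds model or a stratified rank (van Elteren) test. Time to dialysis independence, with those two events counted as not recovered, is an acceptable alternative. Report duration among DGF patients by arm as description only, without a treatment test.

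The cost is mainly wording in the analysis plan. The new analysis uses the end of dialysis dependence, which any measure of duration already needs; the assessment schedule was not legible in the text available, so its capture should be confirmed. There are two drawbacks: the effect is no longer a ratio of mean durations, and the endpoint becomes a composite with primary non-function and death. Both should be stated when it is reported.
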